## Abstract

**Background:** Older hypertensive adults are at increased risk for postoperative morbidity and mortality. As first line antihypertensive drug therapy, angiotensin-converting enzyme inhibitors (ACEIs) or angiotensin receptor blockers (ARBs) have many beneficial effects. However, the use of ACEIs/ARBs in the perioperative period remains controversial. This study aims to determine the effects of withholding vs. continuing ACEIs/ARBs before non-cardiac surgery on perioperative hypotension and postoperative outcomes in older patients.

**Methods:** In this multicenter, randomized, double-blind, placebo-controlled trial, a total of 2036 patients aged 60–80 years undergoing non-cardiac surgical procedures will be randomly assigned, in a 1:1 ratio, to receive oral ACEIs/ARBs (the ACEIs/ARBs continued group) or inactive placebos (the ACEIs/ARBs withheld group) on the morning of surgery. For both groups, the ACEIs/ARBs will be continued from the first postoperative day. The primary outcome measure is the incidence of perioperative hypotensive events, defined as mean blood pressure (MBP) < 65 mmHg or ≥30% reduction in MBP from baseline during surgery and in a post-anesthesia care unit. The secondary outcomes include duration of perioperative hypotension, intraoperative use of fluids and vasopressors, hypotensive events within postoperative 3 days, and perioperative neurocognitive disorders, major adverse cardiocerebral events (a composite outcome of stroke, coma, myocardial infarction, heart block, and cardiac arrest), and mortality within 30 days after surgery.

**Discussion:** The results of this trial will offer an evidence-based perioperative ACEIs/ARBs therapy for older hypertensive adults undergoing non-cardiac surgery.

**Study Registration:** This study is approved by the Medical Ethics Committee of The First Affiliated Hospital of Soochow University (Approval No. 2020-077-1) and by the institutional ethics review board of each participating center. This protocol is registered at the Chinese Clinical Trials Registry (ChiCTR2000039376).

## Introduction

The era of geriatric surgery has arrived (1, 2). With a rapidly aging global population, increasing numbers of surgical operations are being performed on older adults. While several surgical risk factors increase with age, increasing age itself independently predicts postoperative morbidity and mortality (3). Older patients who undergo surgical procedures present great challenges in the perioperative management. To improve the outcomes after geriatric surgery, intensive efforts are required, including careful preoperative risk assessment, treatment for comorbidities, optimal surgical techniques and anesthesia management, and implementation of enhanced recovery after surgery.

Hypertension is a leading preoperative risk factor among patients of all age groups and dominates in the group aged 50 years and older (3–5). Preoperative hypertension increases the risk of surgical bleeding, stroke, and cardiovascular complications. Tight blood pressure control improves outcome. According to the 2017 American College of Cardiology/American Heart Association Task Force on Clinical Practice Guidelines, blood pressure should be <130/80 mmHg during an antihypertensive drug therapy (6). As first line antihypertensive treatment, angiotensin-converting enzyme inhibitors (ACEIs) or angiotensin receptor blockers (ARBs) produce arterial vasodilatation and reduce blood pressure through the inhibition of the renin–angiotensin aldosterone system (4). Moreover, the use of ACEIs/ARBs exerts many beneficial effects, including improved cardiovascular and renal outcomes in patients with diabetes, decreased mortality in patients with acute kidney injury, and improvement in symptoms and survival in patients with heart failure with reduced ejection fraction (7–10).

Nevertheless, the current evidence does not provide a definitive answer regarding whether ACEIs/ARBs should be continued or withheld in the perioperative setting. While some studies showed that continuation of ACEIs/ARBs was associated with an increased risk of intraoperative hypotension (11–15), other studies argued that different ACEIs/ARBs management strategies did not affect perioperative hemodynamic stability or postoperative outcomes (16–19). To date, there is no well-designed randomized controlled trial with adequate power to assess the perioperative risks and benefits of ACEIs/ARBs.

Therefore, the present study aims to determine the effects of withholding vs. continuing ACEIs/ARBs before non-cardiac surgery in older hypertensive adults. The primary outcome measure of this study is the incidence of perioperative hypotension that occurs during surgery and in a post-anesthesia care unit (PACU). The secondary outcome measures include duration of perioperative hypotension, intraoperative use of fluids and vasopressors, and hypotensive events within postoperative 3 days, as well as neurocognitive function, cardiocerebral outcomes, and mortality within 30 days after surgery. We will mainly test the hypothesis that the withholding of ACEI on the day of surgery will decrease the number of perioperative hypotensive events in patients undergoing non-cardiac surgery.

## Materials and Methods

### Study Design

This study is a multicenter, randomized, double-blind, placebo-controlled trial conducted at six tertiary hospitals in China. The leading site is The First Affiliated Hospital of Soochow University, and the participating sites are Zhongshan Hospital Fudan University, Fudan University Shanghai Cancer Center, Shanghai General Hospital, The First Affiliated Hospital of Zhengzhou University, and The First Affiliated Hospital of Anhui Medical University.

### Ethics and Dissemination

The study protocol is approved by the Medical Ethics Committee of The First Affiliated Hospital of Soochow University (Approval No. 2020-077-1) and by the institutional ethics review board of each participating center. This study is registered at the Chinese Clinical Trials Registry on October 25, 2020 (http://www.chictr.org.cn, identifier: ChiCTR2000039376), before the enrollment of the first subject. This study follows the Declaration of Helsinki and the International Conference on Harmonization guidelines for Good Clinical Practice. This report follows the Standard Protocol Items: Recommendations for Interventional Trials (SPIRIT) statement (20).

### Participants

At each study center, an independent preoperative investigator who is not involved in patient care or data management will screen patients' admission records to identify potentially qualified participants. Patients who meet the eligibility criteria and provide their written informed consent will be included in this study. According to the sample size estimation, a total of 2,036 eligible patients who plan to undergo non-cardiac surgical procedures will be randomly assigned, in a 1:1 ratio, to an ACEIs/ARBs continued group or an ACEIs/ARBs withheld group. Patients can withdraw their consent at any time during this study. The patient recruitment started on November 1, 2020. The expected date for completion of recruitment is December 2023. The flow chart of participants is shown in Figure 1.

**Figure 1 F1:**
[figure not shown]
Flow chart of participants. ACEIs/ARBs, angiotensin-converting enzyme inhibitors or angiotensin receptor blockers.

### Inclusion and Exclusion Criteria

Patients are eligible for this trial if they are 60–80 years old with ASA physical status II or III, receiving regular ACEIs or ARBs therapy for hypertension for more than 2 weeks, who are scheduled for non-cardiac surgery under general anesthesia.

The exclusion criteria are as follows: (1) unplanned or emergent surgery, (2) spinal and/or epidural anesthesia, (3) ACEIs/ARBs use only in the evening, intermittent ACEIs/ARBs use, or concomitant use of ACEIs and ARBs, (4) uncontrolled hypertension defined as systolic blood pressure (SBP) ≥ 180 mmHg or diastolic blood pressure (DBP) ≥ 110 mmHg, (5) baseline mean blood pressure (MBP) ≤ 65 mmHg, (6) intravenous use of vasoactive agents, (7) severe cardiopulmonary or cerebrovascular disease, (8) liver or kidney dysfunction (Child-Pugh grade ≥ B, creatinine ≥ 200 μmol/L), or (9) rejection of participation.

### Randomization and Blinding

An independent biostatistician who is not involved in the following study or data management generated a randomization sequence with a 1:1 ratio, permuted block sizes of 2 and 4, and stratification according to study center. Randomization is implemented by using a web-based central randomization system, and allocation concealment is ensured by password protection.

According to the random codes, an independent research nurse will prepare the study medications (either ACEIs/ARBs or inactive placebos) in identical capsules, which were kept in bags labeled with the study numbers and “Antihypertensive agent.” Subjects who meet the eligibility criteria will be randomly assigned to either an ACEIs/ARBs continued group or an ACEIs/ARBs withheld group. The participants, anesthesiologists, surgeons, investigators responsible for data collection, and other healthcare providers will remain masked to treatment allocation until the completion of final analysis.

In case of a severe adverse event considered to be related to study interventions, the attending anesthesiologists or physicians should notify the principal investigator to decide whether unmasking of treatment allocation is needed, and such an event will be documented by an independent data monitoring committee (DMC).

### Study Interventions and Anesthesia

The schedule of enrollment, interventions, and assessments in accordance with the SPIRIT 2013 statement is shown in Table 1. The baseline blood pressure is obtained by independent nursing personnel when patients are comfortably seated in surgical wards before the day of surgery. According to the web-based centralized randomization list, patients will take the study medications (either the ACEIs/ARBs or placebo pills) orally on the morning of surgery. The time of study medication will be documented.

**Table 1 T1:** Schedule of enrollment, interventions, and assessments.

		**Study period**							
	**Enrollment**	**Allocation**	**Post-allocation**						**Close-out**
**Timepoint**	**Preanesthetic visit**	**Prior to surgery**	**During surgery**	**PACU**	**POD 1**	**POD 2**	**POD 3**	**Hospital discharge**	**POD 30**
**Enrollment**									
Inclusion criteria	×								
Exclusion criteria	×								
Informed consent	×								
Demographics	×								
Comorbidities	×								
Randomization	×								
Allocation		×							
**Interventions**									
ACEIs/ARBs continued		×							
ACEIs/ARBs withheld		×							
**Assessments**									
Baseline blood pressure		×							
Hypotension events			×	×	×	×	×		
Other hemodynamic events			×	×	×	×	×		
Fluids and vasoactive agents			×	×					
Intraoperative adverse events			×						
Pain, analgesic use, PONV				×	×	×	×		
ICU admission								×	
Length of postoperative stay								×	
PND, MACE, and mortality				×	×	×	×	×	×

According to SPIRIT 2013 statement of defining standard protocol items for clinical trials.

ACEI, angiotensin converting enzyme inhibitor; ARB, angiotensin receptor antagonist; PONV, postoperative nausea and vomiting; PND, neurocognitive disorders; MACE, major adverse cardiocerebral events; POD, postoperative day.

In the operating room, patients will receive a standard monitoring including heart rate (HR), non-invasive blood pressure, and pulse oximetry. Induction of general anesthesia will be performed with sufentanil 0.2–0.4 μg/kg and etomidate 0.2–0.3 mg/kg. Tracheal intubation will be facilitated with rocuronium 0.6 mg/kg or cisatracurium 0.2 mg/kg. Mechanical ventilation will be performed with a tidal volume of 8–10 ml/kg, frequency of 12–18 breaths/min, adjusted to maintain end-tidal CO_2_ values within 30–40 mmHg. General anesthesia will be maintained with propofol infusion titrated to bispectral index (BIS) values within 40–60, or with sevoflurane inhalation titrated to end-tidal minimal alveolar concentration within 0.8–1.3. To provide adequate intraoperative analgesia and neuromuscular blockade, additional doses of sufentanil and rocuronium (or cisatracurium) can be administered. Body temperature will be maintained at 36–37°C with a nasopharyngeal probe by using a warming blanket and/or an infusion heating device. Other perioperative management will be left to the discretion of the attending anesthesiologists according to the routine practice of each study center. After tracheal extubation, patients will be transferred to the PACU. When a modified Aldrete score ≥ 9 is achieved, patients will be discharged from the PACU to the surgical wards.

For both groups, the use of ACEIs/ARBs will be continued in the morning of the first post-operative day. If a perioperative hypertensive event occurs during the study period, patients will receive antihypertensive treatments based on the institutional clinical practice.

### Outcome Measures

The primary outcome measure of this trial is the incidence of perioperative hypotensive events, defined as MBP <65 mmHg or ≥30% reduction in MBP from baseline for which an intervention is needed (including intravenous fluids infusion and/or use of vasopressors), which occur during surgery and in the PACU.

The secondary outcome measures are: (1) duration of perioperative hypotension, (2) intraoperative use of fluids and vasopressors, (3) postoperative hypotensive events in the surgical wards within 3 days after surgery, and (4) perioperative neurocognitive disorders (PND), major adverse cardiocerebral events (MACEs, a composite outcome of permanent or transient stroke, coma, myocardial infarction, heart block, and cardiac arrest), and mortality within 30 days after surgery. MACE will be assessed as a composite outcome, and each complication will also be assessed individually, according to the definitions in Table 2.

**Table 2 T2:** Definitions of postoperative complications.

**Event**	**Definition**
PND	Indicates perioperative neurocognitive disorders assessed using the CAM-ICU until ICU discharge or using the CAM in the surgical wards and at 30 days after surgery.
MACEs	Indicates a composite outcome of permanent or transient stroke, coma, myocardial infarction, heart block, and cardiac arrest.
Stroke	Indicates a postoperative stroke (i.e., any confirmed neurological deficit of abrupt onset caused by a disturbance in blood supply to the brain).
Coma	Indicates a new postoperative coma that persists for at least 24 h secondary to anoxic/ischemic and/or metabolic encephalopathy, thromboembolic event or cerebral bleed.
Myocardial infarction	Indicates a myocardial infarction event documented by at least one of the following criteria: 1. evolutionary ST-segment elevations; 2. development of new Q-waves in two or more contiguous ECG leads; 3. new or presumably new left bundle branch block pattern on the ECG; 4. cardiac Troponin I > 0.05 ng/ml.
Heart block	Indicates a new heart block requiring the implantation of a permanent pacemaker of any type prior to discharge.
Cardiac arrest	Indicates an acute cardiac arrest documented by one of the following: 1. ventricular fibrillation; 2. rapid ventricular tachycardia with hemodynamic instability; 3. asystole.

*PND, perioperative neurocognitive disorders; MACEs, major adverse cardiocerebral events; CAM, confusion assessment method; ICU, intensive care unit; ECG, electrocardiogram*.

The exploratory outcomes are as follows: (1) the incidence of hypertensive events (MBP > 110 mmHg or ≥ 30% increase in MBP from baseline) during surgery, in the PACU, and within 3 postoperative days, (2) tachycardia or bradycardia events defined as HR > 100 beats/min or HR <50 beats/min, (3) intraoperative adverse events (arrythmia, hypoxia, allergic reaction, major bleeding, hyperthermia, hypothermia, oliguria, acid-base disturbances, electrolyte disorders, lactic acidosis, and cardiac arrest), (4) Ramsay sedation scores in the PACU, (5) numerical rating scale scores for pain, analgesic consumption, and postoperative nausea and vomiting (PONV) in the PACU and in the wards within three post-operative days, (6) time to extubation, (7) intensive care unit (ICU) admission, and (8) length of postoperative hospital stay.

### Data Collection

Patients' demographics, baseline characteristics, and intraoperative data will be collected in the Case Report Forms by independent investigators. Trained postoperative assessors who are unaware of group allocation will collect postoperative in-hospital data by ward visits and 30-day follow-up data *via* telephone. The lead investigator of each study center is responsible for the accuracy and completeness of data. Site visits will be carried out by two investigators for source data verification during the implementation of this study. After de-identification, all data will be stored electronically in a web-based database (https://www.91trial.com/) and monitored by the independent data monitoring committee.

### Sample Size Estimation

The sample size calculation was performed using the PASS software (version 11.0.7, NCSS, LCC, Kaysville, UT, USA). Based on an international prospective cohort study of 4802 patients undergoing non-cardiac surgery, the incidence of intraoperative hypotensive events was 28.6% in the ACEIs/ARBs continued group (15). We hypothesize that the suspension of ACEIs/ARBs before surgery would reduce the incidence of hypotension by 20%, that is, to a hypotension rate of 22.88%. To detect such a difference with α = 0.05 and power = 80%, 916 patients per group are needed. We estimate a drop-out rate of 10%, and thus 1,018 patients will be enrolled in each group.

### Statistical Analysis

Data distribution and normality will be assessed with Shapiro-Wilk test. Continuous variables will be presented as mean ± standard deviation or median (interquartile ranges), depending on their distribution. Categorical variables will be presented as number (percentages). All analyses will follow the intention-to-treat principle, which includes all participants after randomization and excludes the patients who drop out of the study due to withdrawal of informed consent or cancellation of surgery. The per-protocol analysis will be carried out as a sensitivity analysis, which includes all participants with planned interventions and minimal protocol violation. As we expect that the missing data will be uncommon in our dataset, there will be no plan for imputation of missing data.

The primary outcome of perioperative hypotension occurrence will be assessed using multivariate logistic regression adjusting for the following baseline covariates: age, body mass index, ASA status, hypertension grade, previous myocardial infarction, atrial fibrillation, diabetes mellitus, hemoglobin value, use of diuretics, and trial site. The odds ratio with 95% confidence intervals will be reported.

In addition, subgroup analyses for the primary outcome will be conducted to explore whether the effects of study interventions will vary, according to six variables: age, hypertension grade, diabetes mellitus, type of surgery, duration of surgery, and trial site. The interaction analysis of effects across the subgroups will be performed using a test of treatment-by-covariate interaction on a logistic regression model.

For the secondary outcomes, analysis will be conducted using generalized linear model for continuous variables or using multivariate logistic regression for binary variables, adjusting for the above-mentioned baseline covariates. The Benjamini-Hochberg procedure will be used to control the false-discovery rate for multiple comparisons. The *P*-values before and after correction will be presented. For the exploratory outcomes, only descriptive statistics will be applied, without multiple testing or statistical inference.

It is expected that the risk of the study interventions will not be significantly higher compared to the standard medical practice, and there is no ethically risk associated with the primary outcome assessment. Hence, interim analysis will not be performed. All analyses will be done using the SAS software (version 9.4, SAS Institute Inc., Cary, NC, USA) and R statistical software (version 3.6.0, R Foundation for Statistical Computing, Vienna, Austria), with a two-sided *P*-value < 0.05 indicating a statistically significant difference.

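### The set called intention-to-treat drops randomised patients for later events, and the consent-withdrawal rule discards primary outcomes already recorded

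*Protocol article*

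**What the plan says.** The Statistical Analysis section of the protocol article applies intention-to-treat to all analyses and describes the set as everyone randomised. The same sentence then "excludes the patients who drop out of the study due to withdrawal of informed consent or cancellation of surgery". On missing data it expects few gaps and says "there will be no plan for imputation of missing data". Its one stated sensitivity analysis is per-protocol.

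Four other places bear on this:

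- **Participants:** consent may be withdrawn at any point in the study.
- **Table 1 and Study Interventions and Anesthesia:** randomisation is listed at the preanesthetic visit, and "patients will take the study medications (either the ACEIs/ARBs or placebo pills) orally on the morning of surgery". The time of intake is documented.
- **Outcome Measures:** the primary outcome covers surgery and the PACU stay. Follow-up for complications and death runs to day 30.
- **Sample Size Estimation:** "We estimate a drop-out rate of 10" per cent, without giving reasons for the drop-out.

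**The concern.** Consent withdrawal and cancelled surgery both happen after randomisation. A set that leaves these patients out is a modified intention-to-treat set, and the label hides that. The two exclusions differ in weight.

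**Consent withdrawal.** A patient who withdraws on the ward, or during the 30 days, already has a complete primary outcome. The rule removes that patient anyway. Withdrawal may follow a difficult perioperative course, so the loss may be related to the outcome.

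**Cancelled surgery.** A cancellation before the capsule cannot depend on what the capsule contains. A cancellation after it could, because the capsule holds either a blood-pressure drug or placebo.

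If removal is related to outcome and differs between arms, the randomised comparison is no longer protected. Nothing stated in the plan would reveal this, since the per-protocol analysis narrows the set further.

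**Working it through.** **Inputs.** From Sample Size Estimation: "the incidence of intraoperative hypotensive events was 28.6% in the ACEIs/ARBs continued group"; withholding "would reduce the incidence of hypotension by 20%, that is, to a hypotension rate of 22.88" per cent; "To detect such a difference with α = 0.05 and power = 80%, 916 patients per group are needed"; 1,018 enrolled per group. From Statistical Analysis: "two-sided *P*-value < 0.05 indicating a statistically significant difference". The document gives neither the number removed under the rule nor their risk of hypotension. Both are assumed below.

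**1. The plan's own figures.** With p1 = 0.286, p2 = 0.2288, mean 0.2574 and difference 0.0572:

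n = [1.960 × √(2 × 0.2574 × 0.7426) + 0.842 × √(0.286 × 0.714 + 0.2288 × 0.7712)]² / 0.0572² = 916 per group.

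916 / 0.90 = 1,018 per group. Both figures reproduce. Power is 80.0% with 916 per group and 84.0% if all 1,018 are analysed. The allowance of 1,018 − 916 = 102 per group protects power. It does not protect against selective removal.

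**2. The order of events.** Randomisation, then capsule, then surgery, then PACU (primary outcome complete), then ward, then day 30. Consent can be withdrawn at any of these steps. Every withdrawal after the PACU removes an observed primary outcome. A cancellation can fall before or after the capsule, and only the second kind can depend on treatment.

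**3. Shift in one arm's rate.** Let the patients kept have rate r and the removed fraction f have rate r + d. The whole-arm rate is (1 − f) × r + f × (r + d) = r + f × d, so removal shifts the rate by f × d. For a cancelled patient, r + d can only mean the risk had surgery gone ahead.

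| f removed (assumed) | d (assumed) | Shift | Share of 5.72 points |
|---|---|---|---|
| 2% | 20 points | 0.4 points | 7% |
| 10% | 10 points | 1.0 points | 17% |
| 10% | 20 points | 2.0 points | 35% |

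The bias in the risk difference is the gap between the two arms' shifts. Equal shifts cancel.

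**4. Effect on the test.** Assume no true effect, 28.6% in both arms, 102 removed per arm, and removal unrelated to outcome in the continued arm. If those removed from the withheld arm had a 40% risk, the rate among those kept is (0.286 × 1,018 − 0.40 × 102) / 916 = 27.3%. The spurious difference is 1.3 points, and the two-sided type I error is about 9%. At a 50% risk these become 2.4 points and about 21%. With 20 removed per arm (2%), risks of 40 to 60% give 0.2 to 0.6 points and 5.1 to 6.1%.

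**5. Tipping point.** Suppose the planned effect is seen among those kept and the removed patients are restored. With 1,018 per arm, the difference that just reaches p = 0.05 is 3.80 points. The restored withheld patients would need a risk above that of the restored continued patients by (5.72 × (1 − f) − 3.80) / f. This is about 13.5 points for f = 10%, 33 points for 5% and 90 points for 2%.

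**The case against.** The strongest defence has four parts.

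- **Masking.** Patients, anesthesiologists, surgeons and data collectors are masked, so nobody can exclude on known allocation. The article contains no rule for cancelling surgery on blood pressure, and eligibility already removes uncontrolled hypertension and low baseline pressure. This limits the treatment-dependent route. It does not close it, because masking does not stop a decision that responds to the drug's effect.
- **No outcome window.** A patient whose surgery is cancelled has no surgical or PACU period in which the primary outcome could occur. This stands. Leaving such patients out of the primary analysis is defensible under a correct label, and scoring them as hypotension events would not be meaningful.
- **Reporting.** The article commits to CONSORT, so some account of exclusions by arm may follow anyway. That covers part of the reporting request but leaves the rule unchanged.
- **An unseen analysis plan.** Detail may sit elsewhere. This does not help, because the exclusion rule is stated here and is wrong as stated.

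A reader might infer three stronger things that the article does not support. The first is that up to 10% of patients will leave selectively by arm. The 10% is an all-cause planning allowance, neither tied to these two reasons nor a ceiling, and arm-selective loss is not shown. The second is that records with a missing covariate will be deleted. That would be the usual result of fitting a logistic model with ten covariates and no imputation, but no complete-case rule is written. The third is that 10% drop-out contradicts an expectation of few missing data. Drop-outs can leave the analysed set while the data of those who remain are nearly complete.

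**Conclusion.** The point holds in a limited form. The set is mislabelled, and the consent-withdrawal exclusion discards primary outcomes that may already be observed. That follows from the stated rule and needs no assumption. No stated sensitivity analysis brings these patients back.

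Whether the comparison would be biased, and by how much, is not known. With about 2% removed the effect is small: 0.4 points even with a 20-point gap in risk. With 10% removed from one arm and a gap of 10 to 20 points, it is 1.0 to 2.0 points, or 17 to 35% of the planned 5.72, if the other arm shows no matching shift. These are illustrations under assumed inputs, not estimates. The sample size of 2,036 is sound for its stated inputs and is not affected.

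**What to change.** 1. Name the primary set modified intention-to-treat: all randomised patients in whom anaesthesia was started, analysed as randomised.
2. Keep every outcome observed before a withdrawal, unless the patient revokes use of the data.
3. Report exclusions by arm, with reason and timing relative to the capsule.
4. Add a sensitivity analysis on all randomised patients who had surgery, with multiple imputation of missing primary outcomes and a tipping-point analysis. Keep patients with a missing baseline covariate by simple imputation.
5. Mortality and the cardiocerebral composite in cancelled patients may be added as a supportive analysis, but only with a time origin such as randomisation. The current definitions count from surgery, which these patients do not have.

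The cost is a change of wording, one disposition table and one sensitivity analysis. Capsule time is already documented; the date, time and reason of each withdrawal or cancellation must also be on record. The optional analysis in item 5 needs 30-day follow-up of cancelled patients. The sample size stays the same. The change should be made before unmasking, since an analysis set chosen afterwards would not be credible.

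### The primary model's fixed covariate list leaves out measured baseline MBP, which helps define the endpoint; adding it, with risk-scale estimates beside the odds ratio, is a free but modest improvement

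*Protocol article*

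**What the plan says.** All references are to the protocol article.

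- **Endpoint (Outcome Measures).** An event is an MBP below 65 mmHg, or a fall of 30% or more from baseline MBP, that calls for fluids or vasopressors, during surgery or in the PACU.
- **Baseline measurement (Study Interventions and Anesthesia).** "The baseline blood pressure is obtained by independent nursing personnel when patients are comfortably seated in surgical wards before the day of surgery". Table 1 lists it as an assessment before surgery.
- **Primary model (Statistical Analysis).** Logistic regression "adjusting for the following baseline covariates: age, body mass index, ASA status, hypertension grade, previous myocardial infarction, atrial fibrillation, diabetes mellitus, hemoglobin value", then diuretic use and trial site. That makes ten named covariates. The same list serves the secondary outcomes.
- **Effect measure (Statistical Analysis).** "The odds ratio with 95% confidence intervals will be reported". Binary data are otherwise summarised as counts and percentages.
- **Planned effect (Sample Size Estimation).** Withholding "would reduce the incidence of hypotension by 20%, that is, to a hypotension rate of 22.88" per cent.
- **Purpose of adjustment (Discussion).** Adjustment is presented as a strength of the trial, chosen to gain precision and based on known associations between the covariates and outcome.

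**The concern.** A baseline value that enters the endpoint definition is an obvious candidate for adjustment. It is already collected, and the event cannot be scored without it. The list keeps hypertension grade, a category, and leaves out the measurement itself. As the list is named and closed, this is a choice the article makes and not a detail it leaves open. What is at stake is some of the efficiency that the Discussion gives as the reason for adjusting.

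The second part concerns interpretation. The trial is sized on a change in risk, but the only effect measure named is a covariate-adjusted odds ratio. With an event rate near 29%, an odds ratio and a risk ratio differ visibly, and the adjusted odds ratio is also conditional on the covariates. Readers would have no interval on the scale used to plan the trial.

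**Working it through.** **1. The plan's own sample size.** Inputs from Sample Size Estimation: "the incidence of intraoperative hypotensive events was 28.6% in the ACEIs/ARBs continued group"; 22.88% under withholding; "To detect such a difference with α = 0.05 and power = 80%, 916 patients per group are needed". The test is two-sided (Statistical Analysis: "two-sided *P*-value < 0.05 indicating a statistically significant difference").

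n = [1.960·√(2·p̄·q̄) + 0.8416·√(p1·q1 + p2·q2)]² / (p1 − p2)², with p̄ = (0.286 + 0.2288)/2 = 0.2574.

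- First term: 1.960 × √(2 × 0.2574 × 0.7426) = 1.2118
- Second term: 0.8416 × √(0.286 × 0.714 + 0.2288 × 0.7712) = 0.5193
- n = (1.2118 + 0.5193)² / 0.0572² = 915.9, so 916 per group
- Drop-out: 916/0.90 = 1,017.8, so 1,018 per group and 2,036 in total, which agrees with "We estimate a drop-out rate of 10%, and thus 1,018 patients will be enrolled in each group"

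The sample size reproduces exactly and uses no covariates.

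**2. How baseline MBP enters the endpoint.** The pressure component of the threshold is max(65, 0.70 × baseline MBP).

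- Change point: 65/0.70 = 92.9 mmHg.
- Upper end: with SBP below 180 and DBP below 110 (exclusion criteria), and taking MBP as DBP + (SBP − DBP)/3, an assumption, 179/109 gives 132.3 mmHg. The threshold is then 0.70 × 132.3 = 92.6 mmHg.
- Share of patients above the change point, for an assumed normal baseline with mean 95 to 105 and SD 10 to 12: about 57% to 89%.

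Suppose the lowest pressure rises by b mmHg per mmHg of baseline. The margin between lowest pressure and threshold then changes by b below 92.9 mmHg and by b − 0.70 above it. For b = 0.2, 0.4 and 0.6 the upper slope is −0.5, −0.3 and −0.1. The relation changes sign at the change point, so one straight-line term fits poorly, and the information in baseline MBP shrinks as b nears 0.70.

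**3. What the omission costs.** The article gives no MBP distribution or prognostic strength, so everything in this step is assumed.

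- *Validity.* With a covariate of OR 2.0 per SD left out and no treatment effect, 2,000 simulated trials of 916 per group rejected in 5.05%.
- *Power, covariate against no covariate* (1,500 runs each, planned rates, so about ±1 point of simulation error per figure):

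| Assumed OR per SD | Conditional OR | Power without | Power with |
|---|---|---|---|
| 1.3 | 0.738 | 81% | 81% |
| 1.5 | 0.734 | 82% | 83% |
| 2.0 | 0.721 | 80% | 83% |
| 2.5 | 0.708 | 80% | 84% |

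- *Gain beyond hypertension grade.* Assume baseline mean 100, SD 8 to 12, b from 0.2 to 0.6, and residual SD of the lowest pressure 8 to 10. Measure the gain as the squared ratio of the treatment z-statistics, minus 1. It is about 0 to 7% if grade tracks measured baseline closely and up to about 17% if it does not. The larger values arise at b = 0.2; many settings fall below 5%. On 916 per group, 5% is 0.05 × 916 ≈ 46 patients and 17% is 0.17 × 916 ≈ 156.
- *Where the gain comes from.* The standard error of the log odds ratio rises slightly (ratio 1.003 to 1.09). Power improves because the conditional odds ratio moves further from 1, not because its interval narrows.

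**4. Odds ratio against risk ratio.**

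- RR = 0.2288/0.286 = 0.80; risk difference = 5.72 points.
- Marginal OR = (0.2288/0.7712)/(0.286/0.714) = 0.2967/0.4006 = 0.741.
- An OR of 0.80 gives odds 0.80 × 0.4006 = 0.3204 and risk 0.3204/1.3204 = 24.3%, a reduction of about 15%, not 20%.
- At an assumed control rate of 50%, an OR of 0.741 corresponds to an RR of 0.85.

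**The case against.** The strongest reply is that nothing here is an error. Leaving a prognostic covariate out of a randomised comparison preserves the test, and the stated 80% power comes from an unadjusted calculation. That stands, and it limits the severity.

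The event also requires that treatment was needed, so baseline MBP does not determine it mechanically, and for patients below about 93 mmHg the fixed limit governs. Both points stand. A reader might infer that baseline sets every patient's threshold; the definition does not support that. Below the change point, baseline still fixes how far pressure must fall to reach 65 mmHg.

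Hypertension grade may already carry much of the information. This is possible and cannot be tested from the article, which is why the range starts near zero.

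On the effect measure: an odds ratio of 1 and a risk ratio of 1 are the same null, the article never reads the odds ratio as a risk ratio, crude percentages will be shown, and further measures could sit in an analysis plan that is not at hand. So the odds ratio is not wrong. What remains is that the planned effect is on the risk scale and the one named estimate is not.

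A reader might also infer that type of surgery should be added because it is a subgroup variable. The article defines no categories and gives no figure for it, and subgroup use does not oblige adjustment. That change is not proposed.

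**Conclusion.** The point holds as an optional to minor improvement. The closed covariate list omits a measured baseline value that enters the endpoint definition, which fits poorly with the Discussion's own reason for adjusting. The likely cost is small: roughly 0 to 17% of effective sample size beyond hypertension grade, often under 5%, conditional on the assumed MBP distribution, the assumed slope of lowest pressure on baseline, and how closely grade follows measured pressure.

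A reader might infer bias, a faulty type I error rate or an underpowered trial. None follows: randomisation protects the comparison, the simulated error rate is 5.05%, and 916, 1,018 and 2,036 all reproduce.

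The scale mismatch needs none of the MBP assumptions, since RR 0.80 and marginal OR 0.741 follow from the plan's own rates. It affects how the result is read, not whether the test is valid.

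**What to change.** Before unblinding:

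1. Add continuous baseline MBP to the primary logistic model in a form that allows non-linearity: a restricted cubic spline, or a piecewise linear term with a knot near 93 mmHg. Keep the ten listed covariates.
2. From the same model, average the predicted risks under each assignment over all analysed patients, and report the standardised risk difference and risk ratio with 95% CI beside the odds ratio. State that the odds ratio is conditional on the covariates.

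The cost is a few lines of analysis-plan text and code. No new data or patients are needed and the sample size does not change. Timing matters: made after unblinding, a change of covariates would look data-driven.
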